### Missing data

Sample size and power calculations were completed under the assumption of 20% attrition for primary outcome analyses. Thus, while we anticipate missing data, we still expect adequate power to detect differences between study arms. We will examine rates of missing data for all variables and determine whether rates vary by participant characteristics, Judy Center program, or study arm. These analyses will indicate the extent to which missing data could bias results. We will attempt to collect data at each time point regardless of participants’ engagement in earlier data collection efforts. To minimize missing data due to loss to follow-up, we will devote considerable attention to promoting study retention. The planned mixed effects models are generally robust for unbalanced data across study time points. However, we plan to apply multiple imputation to test for bias introduced by missing data in sensitivity analyses; we will impute at least five datasets to generate an estimated average intervention effect.

We plan to perform all analyses using both the intent-to-treat (ITT) approach and a dose–response approach (treating dosage as a continuous variable of 0–10 sessions attended), adjusted for propensity scores. The dose–response approach will examine the relationship between number of MB-VG sessions attended (dosage) and outcomes, using propensity scores to match intervention participants to control-group participants with a similar propensity to take up a given level of intervention. This will reduce the influence of self-selection bias in intervention take up on the estimates of dosage effects. We plan to stratify analyses by whether participants are prenatal vs postpartum and whether participants are primiparous or multiparous.

Interim analysis will be performed to ensure safety. This analysis will focus on whether participating in the intervention has any significant iatrogenic effects. Individuals who score > 40 on the CES-D at any assessment timepoint will be flagged, since this level of symptomatology can be considered “very severe”; these participants will be contacted by the research team per procedures described below in the " Safety considerations and procedures" section. The safety analysis dataset will include those participants who had at least one session of the study intervention. No other formal planned interim analyses are planned.

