*Effectiveness outcomes*: Aim 1 will be tested by examining the coefficient of the treatment vs. control indicator in the random effects model. We will include random intercepts for group and instructors and will also investigate whether a random slope for group is appropriate for the intervention effect. Intervention group, covariates measured at pretest (especially the pretest measures of the outcome, as available), the Judy Center the participant was recruited from, and instructor characteristics will be included as fixed effects. Likelihood ratio tests (significance criterion, *p* < 0.05) will be used to simplify the models following a backward selection strategy. Although the primary analyses will consider each set of follow-up outcomes separately, controlling for pre-test measures in each analysis, we will also consider the use of longitudinal growth models to model the growth in knowledge over the three time points. Primary endpoint #1 is depressive symptoms, as measured by the Center for Epidemiologic Studies-Depression scale (CES-D). A total continuous score (0–60) is calculated for the CES-D. Primary endpoint #2 is depressive episodes as measured by the SCID. The SCID is used to assess the presence/absence of major depression, making it a binary outcome (yes/no). Primary endpoints #3 and #4 are parenting self-efficacy measured via the PACOTIS and parenting responsiveness measured via the MIRI and PCOS (used as a separate coding system when coding the DB-DOS observation assessment). A mean score is calculated for each of the PACOTIS and MIRI subscales. Secondary endpoint #1 is anxiety symptoms, measured via the GAD-7. A total continuous score is calculated for the GAD-7. Secondary endpoint #2 is perceived stress, measured via the PSS-10. A total continuous score is calculated for the PSS-10.

Covariates will be finalized in a Statistical Analysis Plan but based on our prior studies [80, 87] will include (1) whether participant is a first-time mother (e.g., current number of children = 0 at baseline; (2) education (at least some high school vs less than high school); (3) mental health service utilization (we will control for enrollment with a therapist for counseling at baseline and medication for depression at baseline).

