Outliers will be assessed to determine whether it is a data entry error or some other protocol error. If not, sensitivity analyses will be conducted to assess the impact of the outliers. Because this is an intent-to-treat analysis, non-adherence will not be formally dealt with. Reasons for loss to follow-up will be explored and we will determine if any key factors contributed to dropout or attrition. Results of initial analyses will determine the best method to handle missing data in the main study analyses.

Analysis of the secondary endpoints will be examined in a manner like those described above related to analysis of our primary endpoints. Primary and secondary outcomes will be assessed utilizing mixed effects logistic regression (when outcomes are binary) and mixed effects linear regression (when outcomes are continuous). Subgroup analysis will follow the same analytic protocol, beginning with the addition of an interaction term between intervention status and the subgroup variable. This will be followed by multiple group analysis.

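### The claimed robustness of the mixed models to missing visits does not apply to primary models fitted to one follow-up at a time

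*Protocol article*

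**What the plan says.** The Missing data section relies on the form of the model: "The planned mixed effects models are generally robust for unbalanced data across study time points". It then adds imputation in a supporting role: "we plan to apply multiple imputation to test for bias introduced by missing data in sensitivity analyses", and "we will impute at least five datasets to generate an estimated average intervention effect". It also plans to compare missingness by participant characteristics, Judy Center and arm, and to seek data at every visit whatever a woman did earlier. About 20% attrition is assumed.

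The effectiveness paragraph of the Quantitative analysis section describes the primary models: "Although the primary analyses will consider each set of follow-up outcomes separately, controlling for pre-test measures in each analysis". On random effects it says: "We will include random intercepts for group and instructors". No participant-level effect is named. A joint analysis over time is optional: "we will also consider the use of longitudinal growth models to model the growth in knowledge over the three time points". Knowledge is not among the trial's listed outcomes.

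Later in the same section the main method is left open: "Results of initial analyses will determine the best method to handle missing data in the main study analyses".

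**The concern.** A mixed model copes with incomplete follow-up when each woman contributes all her observed visits and the model carries the correlation between them. Her earlier scores then inform the comparison at a visit she missed. A model for one visit has one row per woman. If that row is missing, she leaves the analysis, and random intercepts for group and instructor do not bring her back.

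With 20% attrition, 0.20 x 300 = 60 women are affected. Because the trial will try to collect every visit, many of them should have another follow-up score in hand. If the reasons for dropping out are tied to earlier scores differently in the two arms, the per-visit comparison is biased although data that could reduce the bias have been collected. The protocol also gives two accounts of what the main missing-data method is: one section names it, and the other leaves it to initial analyses.

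**Working it through.** **The passages side by side.** The Missing data section claims a property across time points. The primary models contain only one time point each, so there is no imbalance across time points for them to be robust to. The property would hold for the growth model, but that model is only to be considered.

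**The plan's own figures.** The Statistical analysis section gives minimal detectable effects of 0.241 (N = 300) and 0.269 (after attrition, N = 240), at 80% power and two-sided alpha 0.05. For 1:1 individual randomization:

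MDES = (t_0.975 + t_0.80) x sqrt[(1 - R2) / (0.25 N)]

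R2 is not stated. Solving for it gives R2 = 0.45, which returns 0.2407 at N = 300 and 0.2693 at N = 240. With R2 = 0 the values would be 0.325 and 0.363. So 0.269 is the figure for 240 completers. That fits an analysis of completers at each visit, though it does not prove one.

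**Size of the possible bias.** The documents give no dropout mechanism or visit correlations, so the following are assumptions:
- 150 women per arm and a true effect of -0.27 SD;
- baseline to follow-up correlation 0.67 (0.67 squared is about 0.45) and correlation 0.75 between follow-ups;
- the 1-week score always observed, and 20% missing at 6 months in each arm;
- where dropout depends on a score, a logit slope of 1 per SD;
- 1,500 simulated trials per setting.

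The separate-visit estimate is the arm coefficient from regressing the observed 6-month score on arm and baseline. The joint-likelihood estimate is b_arm + b_1wk x a_arm. Here b comes from regressing the 6-month score on arm, baseline and 1-week score, and a_arm is the arm effect on the 1-week score.

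| Dropout at 6 months depends on | Separate visit | Joint | Imputation (m = 5) with 1-week score | Imputation (m = 5), arm and baseline only |
|---|---|---|---|---|
| Nothing | -0.270 | -0.270 | -0.270 | -0.270 |
| 1-week score, same in both arms | -0.272 | -0.273 | -0.273 | -0.272 |
| 1-week score, MB-VG arm only | -0.324 | -0.271 | -0.271 | -0.325 |
| 1-week score, opposite in the two arms | -0.380 | -0.270 | -0.269 | -0.380 |
| Unseen 6-month score, MB-VG arm only | -0.366 | -0.339 | -0.339 | -0.366 |
| Unseen 6-month score, opposite in the two arms | -0.470 | -0.414 | -0.415 | -0.470 |

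Bias of the separate-visit estimate when dropout depends on the 1-week score:
- MB-VG arm only: 0.324 - 0.270 = 0.054 SD.
- Opposite in the two arms: 0.380 - 0.270 = 0.110 SD.
- With correlations 0.5 (baseline) and 0.7 (follow-up), the estimates are -0.349 and -0.430, so the bias is 0.079 and 0.160 SD. The joint estimates are -0.270 and -0.269.

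Against the stated 0.269 these are 0.054/0.269 = 20%, 0.110/0.269 = 41% and 0.160/0.269 = 59%. The sign follows the assumed slope; reversing the slope would shrink the apparent effect.

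**Number of imputations.** Relative efficiency is 1/(1 + FMI/m), where FMI is the fraction of missing information. At m = 5 it is 1/(1 + 0.20/5) = 0.96 for FMI 0.20 and 0.94 for FMI 0.30. The Monte Carlo noise in the pooled estimate is about sqrt(FMI/m) standard errors. At FMI 0.20 that is 0.20 for m = 5 and 0.063 for m = 50.

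**The case against.** Several stronger readings are tempting, and the documents do not support them.

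- **That the planned imputation cannot test for bias.** It can. In the table, five imputations that include the 1-week score return -0.27 where the separate-visit model gives -0.32 or -0.38, so comparing the two would expose the problem. Imputation fails if it uses only arm and baseline, or if dropout depends on unseen scores. The article does not list the imputation variables, and that detail may properly sit in the analysis plan.
- **That only five missing-at-random imputations are planned.** Five is a floor, the loss of efficiency there is 4 to 6%, and missing at random is never stated; it is an inference from usual practice.
- **That the primary result will be biased.** A separate-visit analysis is valid if missingness depends only on arm and the model's covariates, and it showed no bias here when the mechanism was the same in both arms. The article predicts no arm-specific dropout. The offer of MB-VG to controls after their last assessment is a difference between arms that could affect retention, but no more than that.
- **That treatment results will pick the missing-data method.** The sentence before the one at issue is about exploring reasons for loss to follow-up, so the initial analyses may be dropout diagnostics. What stands is that the sentence is ambiguous and leaves open a method that the Missing data section appears to have settled.
- **That one joint model suits every endpoint.** It does not. PCOS is collected once, at 6 months. Table 2 lists PACOTIS and MIRI at 3 and 6 months without a baseline, although the Abstract adds a 1-week assessment and the Self-report surveys section has primary outcomes surveyed at all four time points. SCID has two visits. At 1 week there is no earlier follow-up score to borrow from.

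Retention efforts and the missingness checks by arm and center are real safeguards. None of this makes the robustness sentence true of the primary models.

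**Conclusion.** The point holds as a conflict between two sections. The robustness claimed under Missing data is not a property of the primary models described under Quantitative analysis, which drop a woman from any visit she misses and ignore her other follow-up scores. That follows from the text without any assumption.

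The size does rest on assumptions. If dropout depends on an earlier observed score differently by arm, the bias is about 0.05 to 0.11 SD, and up to 0.16 SD with a weaker baseline correlation. It is nil if the mechanism is the same in both arms. A joint model removes this bias but only part of the bias from dropout that depends on unseen scores: in the one-arm case the estimate moves from -0.366 to -0.339 against a truth of -0.27. The article describes no analysis for that situation. The main missing-data method is also stated inconsistently. A reader should not infer that the trial's result will be biased or that the planned imputation is worthless.

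**What to change.** 1. For outcomes with two or more follow-ups (CES-D and the repeated secondary scales; PACOTIS, MIRI and SCID at their scheduled visits), make one joint repeated-measures model primary and read the arm contrast at each visit from it. Include arm by visit, baseline by visit where a baseline score exists, and an unstructured within-woman covariance, or a participant random effect in the logistic model for SCID. Keep a single-visit model for PCOS. If separate models are kept as primary, delete the robustness sentence.
2. Put earlier follow-up scores in the imputation model and use more than five datasets, so that the pooled result depends less on the random seed.
3. Add a delta-adjusted (missing-not-at-random) sensitivity analysis, since imputation under missing at random cannot address dropout that depends on unseen outcomes.
4. Replace the sentence that leaves the main method to initial analyses with a method fixed before any comparison of outcomes by arm. Dropout diagnostics can still be reported.

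The cost is analysis-plan wording and modest extra programming. No new data are needed.

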### Study design

This is a Hybrid Type 1 Implementation-Effectiveness trial designed as a two-arm randomized controlled trial (RCT), with individuals randomized (using REDCap-generated random numbers) via 1:1 allocation ratio to MB-VG or usual Judy Center services followed by delayed intervention receipt (receipt after data collection at 6-month time point). We selected an RCT design given our primary study aim to examine effectiveness of the MB-VG intervention. Women randomized to the usual care arm will be offered participation in MB-VG after completing their final data collection activity at 6 months post-randomization. We recognize this may result in MB-VG being offered beyond the period where there is greatest prevalence of depression among new mothers; however, this approach was endorsed by Judy Center partners. Specifically, they felt that in its absence some women may not consent to participation knowing they may not be able to receive MB-VG.

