#### Usual care

Women randomized to the usual family support services/usual care arm will receive Judy Center services without any MB-VG intervention during the study period (but will receive MB-VG after 6 months via our delayed intervention design, if interested). Judy Centers provide an array of services including parenting education, case management, family health and developmental assessments and referrals, and partnerships with childcare and education providers (e.g., Head Start).

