### Statistical analysis

Power calculations were conducted focusing on the effectiveness aim using maternal self-report of depressive symptoms (measured by the Center for Epidemiologic Studies-Depression scale (CES-D)) and parenting practices (measured by the Parental Cognition and Conduct Towards the Infant Scale (PACOTIS)), assuming power = 80%, a two-tailed test with an alpha of 0.05. To do these power calculations, we used the PowerUp tool. We plan to recruit 300 participants for the trial, 150 participants per condition. Based on these numbers, we expect a minimal detectable effect size of 0.241. Because of the longitudinal nature of the study, we expect some attrition (~ 20%). Accounting for attrition, we can expect a minimal detectable effect size of 0.269. Based on prior research, we expect small to moderate effect sizes, which we will have the ability to detect. We believe clustering by group will be very small and thus do not take it into account in the power analysis. Doing so would lead to a small increase in the minimal detectable effect sizes (e.g., increasing from 0.241 to 0.284).

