### Safety considerations and procedures

Any participant whose responses on the EPDS (or subsequent assessments) indicate that they have had thoughts about their death or suicide within the past month will be asked additional questions to determine the suicidality degree, including whether they have experienced thoughts of their own death, thoughts about suicide, a specific plan or details about how they might take action, and any attempts they have made to hurt themselves. If assessments have been self-administered (e.g., EPDS), participants will via REDCap automatically receive information about 24/7 Spanish-language resources (e.g., National Suicide Prevention Hotline, Postpartum Support International, and the National Maternal Mental Health Hotline). Participants will be required to acknowledge receipt of these resources. In addition, designated study personnel will be immediately alerted by email and text via the survey notification function in REDCap and will reach out to and assess participants within 24 h. In this assessment, participants will be asked additional questions to determine the suicidality degree, including whether they have experienced thoughts of their own death, thoughts about suicide, a specific plan, or details about how they might take action, and any attempts they have made to hurt themselves. Study staff will also reach out to the referring Judy Center to work collaboratively to coordinate referrals for additional services if needed (case management is a core component of the Judy Center). In addition to events prompting safety protocol as above (reporting suicidal ideation on assessments), individuals who have a clinically significant finding of a CES-D score > 40 at any time point will trigger the use of our safety protocol (including text alert to PI via REDCap if completed independently) to ascertain whether there is any risk for self-harm. We will do analysis quarterly to assess for any iatrogenic effects. Text messages in MB-VG are designed to be unidirectional and primarily focused on reminding participants to practice skills and provide reminders about sessions and resources. However, it is possible that participants may respond to messages. Participants will be notified that the system is automated and that it does not constitute direct communication with a provider or therapist. Additionally, the platform will be programmed such that and research staff will be notified via text message and/or email if a keyword is texted via the SMS platform that express potential for self-harm, such as “die,” “suicide,” and “kill”. Additionally, if the participant types one of these keywords, a text message will be automatically sent to the participant like those described above. Prior to initiating the study/intervention, the research team will work with each Judy Center to confirm their client risk assessment procedures, which typically include immediate notification of relevant center staff (e.g., case manager or center director/supervisor), risk assessment, provision of local resources, or emergency referral.

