### Data safety and trial monitoring

An independent Data Safety Monitoring Board (DSMB) has been formed and will meet once per year to monitor adverse events and trial progress. The three-person DSMB is [name] (Chair); [name]; [name]. Protocol modifications will be reported to the DSMB and Johns Hopkins IRB, with any significant protocol changes related to participants’ trial involvement shared with already enrolled study participants.

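### The interim safety dataset requires at least one MB-VG session, so during follow-up it holds no controls against which to judge an iatrogenic effect

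*Protocol article*

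**What the plan says.** The interim safety analysis is described in the Missing data section of the protocol article. Its purpose is given as: "This analysis will focus on whether participating in the intervention has any significant iatrogenic effects". The population follows in the same paragraph: "The safety analysis dataset will include those participants who had at least one session of the study intervention". The paragraph adds that no further formal interim analyses are planned.

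Two other sections settle who can meet that rule. Usual care states: "Women randomized to the usual family support services/usual care arm will receive Judy Center services without any MB-VG intervention during the study period". Study design says that women in the usual care arm "will be offered participation in MB-VG after completing their final data collection activity at 6 months post-randomization".

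The safety data themselves are not limited to one arm. The CES-D trigger reads "Individuals who score > 40 on the CES-D at any assessment timepoint will be flagged", and Safety considerations and procedures has all on-study adverse events logged whatever their relationship to the intervention. That section also says "We will do analysis quarterly to assess for any iatrogenic effects", without naming another dataset or a comparator.

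Missing data and Quantitative analysis both state that every analysis will be done by intention to treat and by a dose–response approach. Missing data explains that the latter matches intervention participants to controls.

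**The concern.** Whether participation causes harm is a causal question. It needs some estimate of what would have happened to the same kind of women without MB-VG. The trial has that estimate in its randomized control arm, but the stated dataset leaves it out.

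Participants are chosen because they are at risk of a major depressive episode, so severe symptom scores and suicidal thoughts can be expected in both arms. With attenders only, an interim reader could take background events for harm, or take harm for background. Dropping assigned women who attend no session adds a second problem: the people analysed are then selected by their own uptake, which the article itself recognises as a source of bias when it plans propensity adjustment for dosage.

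**Working it through.** The article states no figure for this analysis, so there is none to reproduce. The check applies the inclusion rule to each arm and then asks what the resulting dataset can show.

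**Step 1. Who qualifies.** Statistical analysis gives the arms: "We plan to recruit 300 participants for the trial, 150 participants per condition".

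- MB-VG arm: women with one or more sessions qualify, at most 150. Women with none do not.
- Control arm: sessions during the study period = 0 (Usual care), so 0 of 150 qualify.
- A control who later takes up MB-VG could formally enter. Her scheduled assessments all precede her first session, because the offer follows her final data collection (Study design). She contributes no scheduled assessment after exposure and is not a concurrent comparator.

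Usual care cannot meet the rule by another route. It is not described as delivered in sessions, whereas the article counts dosage as 0–10 MB-VG sessions attended.

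**Step 2. What a one-arm proportion can tell.** The article gives no background rate for CES-D above 40 or any other safety event. The rates here are assumptions. Flagged proportion among attenders = background rate × relative risk:

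- 0.05 × 2.0 = 0.10 (risk doubled)
- 0.10 × 1.0 = 0.10 (no effect)
- 0.20 × 0.5 = 0.10 (risk halved)

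The same 10% fits harm, no effect and benefit. Only a control proportion (5%, 10% or 20%) would tell them apart. The argument does not depend on these particular rates.

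**Step 3. What restoring the controls buys.** With all randomized women compared by arm, the comparison is up to 150 v 150, or 150 × (1 − 0.20) = 120 per arm after the article's assumed 20% attrition. Power for a two-sided 5% test of two proportions is

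Φ{ [d − 1.96·√(2·p̄(1−p̄)/n)] / √([p₁(1−p₁)+p₂(1−p₂)]/n) },

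where d = p₂ − p₁ and p̄ is the mean of the two rates. For 5% v 10% and n = 150: p̄ = 0.075; the null standard error is √(2 × 0.075 × 0.925/150) = 0.0304; the alternative standard error is √((0.0475 + 0.09)/150) = 0.0303. Then (0.05 − 1.96 × 0.0304)/0.0303 ≈ −0.32, and Φ(−0.32) ≈ 0.38.

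Power to detect a doubling, over assumed background rates:

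| Background | 150 per arm | 120 per arm |
|---|---|---|
| 2% | 17% | 15% |
| 5% | 38% | 31% |
| 10% | 68% | 58% |
| 15% | 88% | 80% |
| 20% | 97% | 93% |

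These figures use the full sample. An interim look before recruitment ends has fewer women and less power.

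**The case against.** The best defence is that the effect on the trial is narrow. CES-D score and SCID depressive episodes are primary endpoints, compared between arms by intention to treat with two-sided tests, so worsening under MB-VG could appear in the final analysis. Individual protection does not depend on the dataset: the CES-D trigger, the suicidality procedures and adverse-event reporting to the DSMB are not restricted by arm. All of this stands, and it limits the point to interim monitoring. It does not answer the interim question, and two of the three monitored adverse events, suicidal ideation and possible child abuse or neglect, are not listed as efficacy endpoints.

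A second defence is that the general intention-to-treat statement already implies a comparison. It shows that the authors may have intended one. But it contradicts the specific safety-set sentence, and the two have to be reconciled.

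A reader might be tempted to go further in several directions that the article does not support:

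- *That the trial cannot show harm at all.* The final between-arm comparison contradicts this.
- *That within-arm data say nothing.* Change from baseline or by number of sessions can be examined, but it is confounded by the natural perinatal course, regression to the mean and self-selected attendance.
- *That quarterly analysis conflicts with a DSMB that* "will meet once per year to monitor adverse events and trial progress". Quarterly analysis by the study team and annual DSMB oversight are compatible.
- *That by-arm tables would unblind the study team.* The Blinding section blinds those who administer or code named assessments, not the whole team.
- *That weekly sessions detect more events in the MB-VG arm.* No section names sessions as a detection route. The text-message keyword alert is the one route tied to MB-VG.

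**Conclusion.** The safety-set definition is wrong as written for the question it is meant to serve. During follow-up it contains up to 150 MB-VG women and no controls, it omits assigned women who never attend, and it conflicts with the intention-to-treat statement in the same section. This follows from the article's own definitions and rests on no assumed rate; the rates in the illustration and the power table are assumptions. The consequence is confined to the interim safety analysis. Restoring the controls makes the analysis interpretable but not necessarily sensitive: at assumed background rates of 2% to 5%, power to detect a doubling is 17% to 38% even with 150 per arm, so a non-significant result should not be read as evidence of no harm.

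**What to change.** - Define the safety analysis set as all randomized participants, compared by assigned arm up to the final assessment before delayed MB-VG. Remove the conflict with the intention-to-treat statement.
- Base the comparison on measures collected on the same schedule in both arms: CES-D above 40, and suicidal ideation reported on assessments. Show estimates with confidence intervals, not only tests.
- List other logged adverse events by arm, marking those detected only through MB-VG text messaging. Possible child abuse or neglect belongs in this listing, because the table of effectiveness measures (Table 2) names no scheduled instrument for it.
- Keep the at-least-one-session set as a supplementary description of attenders, and report events during delayed MB-VG separately.

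The cost is wording and a little analysis work. CES-D is already scheduled in both arms and adverse-event logging is not restricted by arm, so no new data collection is needed.
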